#### Procedures for SA3 (part 2)

2.2.3

Immediately following the completion of Part 1, a 6.5 min *in-phase* stimulation block will be initiated, with simultaneous hd-EEG and pain monitoring using the NOL index, mean arterial pressure and heart rate. The first minute of *in-phase* stimulation will be free of painful stimulation (*Pre-Pain*). A standardized nociceptive stimulation will then be delivered for 30 s (*Pain*). This will consist in a standardized tetanic stimulation to the ulnar nerve of the non-dominant forearm delivered by a routine nerve stimulator (100 Hz, 70 mA; Life Tech - EZstim II) for a duration of 30 s. Measurements will continue during 5 min following painful stimulation (*Post-Pain*). Upon completion, noise-blocking earmuffs, in-ear earphones, and the hd-EEG net will be removed, and study team will exit the operating room. Surgery will begin and anesthetic procedures will continue as standard of care.

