### EEG pre-processing

3.1

EEG data will be preprocessed using a custom MNE Python script and will be bandpass filtered from 0.1 to 50 Hz. Non-scalp, noisy channels, and channels overlapping with the BIS monitor will be removed. EEG data will be re-referenced to an average reference. Data will then be segmented into the 6 conditions of study: (1) *In-phase*; (2) *Anti-phase*; (3) *sham*; (4) *Pre-Pain*; (5) *Pain*; (6) *Post-Pain*.

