#### Effect of CLAS on *δ*-waves morphology and topography

3.7.1

EEG data will be processed at the level of individual channels to characterize the impact of CLAS on δ-wave morphology and topography using custom Python scripts. Each detected δ-wave will be segmented as a single event (250–10,000 ms duration), and morphology will be quantified by amplitude, slope, transition frequency, density, and power spectral density (Bouchard et al., 2021). These metrics will be compared across conditions (*in-phase*, *anti-phase, sham*) and cortical regions of interest (frontal, central, midline, parietal, temporal, occipital). Descriptive statistics will be computed at both the subject and group level, with comparisons assessed using repeated-measures ANOVA and independent-samples *t*-tests, including age and sex as covariates.

Topographical EEG maps will be generated for canonical frequency bands (delta (0.1–4 Hz), theta (4–8 Hz), alpha (8–13 Hz), beta (13–30 Hz)), and phase-amplitude coupling measures will be calculated to further assess condition-dependent differences in oscillatory dynamics. Topographical mapping will allow testing for regional differences, as frontal predominance of *δ*-waves is a hallmark of both sleep and propofol anesthesia (Murphy et al., 2011; Purdon et al., 2015). To extend beyond scalp measures and as an exploratory aim, source estimation will be performed using standardized head models (Michel and He, 2019). Finally, propagation analyses will be conducted to quantify directionality of δ-wave travel across the cortex, as slow oscillations are known to spread as traveling waves and have been proposed as indices of large-scale cortical communication (Massimini et al., 2004; Tononi and Massimini, 2008).

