#### CLAS and nociceptive stimulation

3.7.3

Because nociceptive stimulation will be delivered only during *in-phase*, the primary analyses will assess within-subject changes across the *Pre-Pain*, *Pain*, and *Post-Pain* epochs. As a first step, *δ*-wave morphology will be quantified by comparing amplitude, slope, and power spectral density (PSD) across the three conditions, since these features provide sensitive markers of cortical arousal and nociceptive disruption under anesthesia (Bonhomme et al., 2016; Plourde et al., 2006). To dissociate band-limited power changes from broadband spectral shifts that can occur under propofol anesthesia, we will additionally parameterize the aperiodic (1/f-like) component of the EEG power spectrum for each stimulation block. Power spectral density will be estimated per block and channel, and the aperiodic exponent (slope) and offset will be extracted over a predefined frequency range using spectral parameterization methods. These aperiodic parameters will be compared across *in-phase, anti-phase*, and *sham* conditions and, where relevant, included as covariates when interpreting *δ*-band power changes.

The primary analysis of nociceptive reactivity will be changes in the NOL index and time-to-recovery. Secondary analysis will examine changes in mean arterial pressure (MAP), heart rate (HR), and BIS index values. Source localization and propagation analyses will further characterize the cortical generators and spatiotemporal spread of δ-waves during nociception (Massimini et al., 2004; Murphy et al., 2011).

Statistical models will include linear mixed-effects analyses with Condition (*Pre-Pain*, *Pain*, *Post-Pain*) as a fixed factor and age, and sex. *p*-values will be corrected for multiple comparisons using familywise error correction. This design enables testing whether *in-phase* CLAS can preserve *δ*-wave integrity and stabilize autonomic reactivity in the presence of nociceptive input, a key criterion for balanced anesthesia (Garcia-Larrea and Bastuji, 2018).

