### Secondary hypothesis (H3): CLAS effects on SWA under nociception

4.3

Under nociceptive input, *in-phase* CLAS is expected to partially enhance *δ*-wave dynamics relative to pain without CLAS, though the magnitude of enhancement will be attenuated compared to non-nociceptive conditions. Specifically, under *in-phase* CLAS, δ-wave morphology should recover faster in *Post-Pain*, with amplitude/PSD returning closer to *Pre-Pain* values than expected absent stimulation. At the network level, nociception may interrupt anterior to posterior spread and temporarily reduce inter-regional coherence, whereas *in-phase* CLAS should stabilize these spatiotemporal dynamics, limiting disruption of fronto-central coherence. We also hypothesize that *in-phase* CLAS will buffer autonomic nociceptive responses, yielding smaller increases in NOL, MAP, and HR during tetanic stimulation and faster return toward baseline afterward (Ben-Israel et al., 2013; Edry et al., 2016), without altering anesthetic/analgesic dosing.

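### SA3 models Post-Pain as one 300 s level, so the δ-wave recovery that H3 predicts is not tested and a brief dip is averaged toward Pre-Pain

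*Protocol article*

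**What the plan says.** Section 2.2.3 (Procedures for SA3) fixes the epochs: "Immediately following the completion of Part 1, a 6.5 min" in-phase block is run, in which the first minute of "stimulation will be free of painful stimulation" (Pre-Pain). The tetanic stimulus is then applied "for a duration of 30 s" (Pain), and "Measurements will continue during 5 min following painful stimulation" (Post-Pain).

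Section 3.1 (EEG pre-processing) makes each epoch one analysis condition: "Data will then be segmented into the 6 conditions of study". No sub-window of Post-Pain is named.

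Section 3.7.3 (CLAS and nociceptive stimulation) compares δ-wave amplitude, slope and PSD across the three epochs. "Statistical models will include linear mixed-effects analyses with Condition" as a three-level fixed factor, plus age and sex; no time term is stated. The same section plans a time-to-recovery analysis for the NOL index.

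Section 4.3 (H3) predicts that, under in-phase CLAS, δ-waves recover more quickly during Post-Pain, with amplitude and PSD ending nearer to Pre-Pain "values than expected absent stimulation".

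**The concern.** H3 is partly a statement about speed, whereas the stated model estimates one average level for five minutes. A dip that fades in the first minute or so is mixed with four minutes of recovered signal. Post-Pain may then look much like Pre-Pain because of the averaging alone. Section 3.7.3 intends to use this comparison to judge whether in-phase CLAS preserves δ-waves under nociception, and the averaging tilts it toward the hoped-for reading.

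**Working it through.** **1. The plan's own figure.** Pre-Pain 60 s + Pain 30 s + Post-Pain 300 s = 390 s = 6.5 min, as stated in section 2.2.3. Post-Pain is 300/30 = 10 times as long as Pain and 300/60 = 5 times as long as Pre-Pain.

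**2. Dilution of the dip.** Assume that the disturbance at the start of Post-Pain has size 1 and decays as exp(−t/τ). Its mean over a window from a to b seconds is τ[exp(−a/τ) − exp(−b/τ)]/(b − a). Over 0–300 s this is τ[1 − exp(−300/τ)]/300. The document gives no τ, so a range is shown.

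| τ (assumed) | 0–300 s mean | first 30 s | first 60 s | last 60 s |
|---|---|---|---|---|
| 15 s | 5% | 43% | 25% | 0% |
| 30 s | 10% | 63% | 43% | 0% |
| 60 s | 20% | 79% | 63% | 1% |
| 120 s | 37% | 88% | 79% | 11% |
| 180 s | 49% | 92% | 85% | 22% |

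**3. Depth and speed are confounded.** A dip of size 1 with τ = 30 s has a 300 s mean of 0.100. A dip of half that size with τ = 60 s has 0.5 × 0.199 = 0.0995. The two recoveries differ twofold in speed, yet the Post-Pain level is practically the same.

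**4. Coherence, only if wPLI is used across these epochs.** SA3 (section 1.8) and H3 refer to coherence under pain without naming a measure. Section 3.4 defines wPLI with a range of 0 to 1. Simulated mean non-negative wPLI for two unrelated Gaussian signals, with independent segments of assumed length:

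| Segment length | 30 s | 60 s | 300 s |
|---|---|---|---|
| 1 s | 0.21 | 0.15 | 0.07 |
| 2 s | 0.29 | 0.21 | 0.09 |
| 4 s | 0.42 | 0.29 | 0.13 |

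With true coupling and 2 s segments, the values were 0.54, 0.54 and 0.55, so the difference nearly vanishes. The debiased squared wPLI at zero coupling was about 0.00 at all three lengths, and mean dPLI about 0.50. The formula printed in section 3.4 has no absolute value in the numerator, despite the stated range; that signed form averages about 0 at zero coupling at any length.

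**The case against.** Several objections are sound and limit the point.

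- **Recovery is not ignored altogether.** A reader might infer that the plan averages away all post-pain recovery. It does not: NOL time-to-recovery is planned. The gap is in the δ-wave outcomes.
- **Unequal length is not itself a bias for the named outcomes.** Mean amplitude, slope, PSD and per-second density are not shifted by epoch length; only their precision changes. The problem is averaging over a changing signal.
- **Phase-lag measures are not assigned to the pain epochs.** A reader might infer that SA3 connectivity will differ by epoch length alone. Section 3.4 sets wPLI per stimulation block, section 3.7.2 places wPLI and dPLI under depth of anesthesia, and the in-phase, anti-phase and sham blocks are equal at 3 min. The wPLI caution is therefore conditional.
- **The wave count is not a defect.** Each wave "will be segmented as a single event (250–10,000 ms duration"), so 30 s could in theory hold only three waves (30/10). That is the extreme of the accepted range, and nothing suggests it is typical.
- **Part of H3 concerns level.** A Pre/Post contrast does address whether amplitude and PSD come back near Pre-Pain, but dilution makes closeness over 300 s easy to reach.
- **The model may take wave-level rows, and an unseen analysis plan may add bins.** Both are possible. Wave-level rows do not help without a time term, because all Post-Pain waves still share one mean. The article does fix the segmentation and the fixed terms. If bins exist elsewhere, the remedy is to align the wording.

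**Conclusion.** The point holds for δ-wave amplitude, slope and PSD. As stated, the model cannot test the recovery course in H3, and a single Post-Pain level understates the initial dip, retaining about 5% to 49% of it for time constants of 15 to 180 s. These percentages rest on an assumed exponential shape and assumed time constants. The direction needs less: whenever the disturbance fades within the five minutes, the mean is smaller than the initial dip.

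A reader might go further and infer that a binned analysis would establish whether CLAS preserves δ-waves under pain. The documents do not support that. Section 3.7.3 says that nociceptive stimulation is given only during in-phase CLAS, so there is no pain-without-CLAS course for comparison. Section 2.2.2 also allows for gradual deepening over time; Post-Pain is centred 90 + 150 = 240 s into the block and Pre-Pain at 30 s, so some change may be drift. Binning shows the course; it does not attribute it.

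**What to change.** In section 3.7.3:

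- Split Post-Pain into successive pre-specified bins: for example ten of 30 s (300/30), or a few wider ones.
- Compare them with Pain and with a Pre-Pain window of equal length, such as its last 30 s if 30 s bins are used.
- Put time in the mixed model for δ-wave amplitude, slope and PSD.
- Test δ-wave recovery as one trend or a small set of contrasts, so that the planned familywise correction is not spread over every bin.
- If fronto-central coherence is measured with wPLI across the pain epochs, use equal-length data or a debiased estimator.
- Report recovery as a within-subject time course, not as an effect of CLAS.

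The cost is analysis wording, preferably settled before the data are examined; no new data or procedures are needed. The drawbacks are noisier single-bin estimates and more contrasts with 30 patients, which wider bins or a single trend test would limit.

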## EEG data analysis

3

### EEG pre-processing

3.1

EEG data will be preprocessed using a custom MNE Python script and will be bandpass filtered from 0.1 to 50 Hz. Non-scalp, noisy channels, and channels overlapping with the BIS monitor will be removed. EEG data will be re-referenced to an average reference. Data will then be segmented into the 6 conditions of study: (1) *In-phase*; (2) *Anti-phase*; (3) *sham*; (4) *Pre-Pain*; (5) *Pain*; (6) *Post-Pain*.

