*Specific Aim 2 (SA2): Characterize the effect of in-phase CLAS on depth of anesthesia, as assessed through clinical monitoring tools and high-density EEG*. We hypothesize that *in-phase* CLAS will be associated with EEG and BIS changes indicative of altered anesthetic depth. At the network level, we expect *in-phase* CLAS to be associated with decreased functional connectivity within fronto-parietal circuits, reduced network integration, and increased modular segregation, consistent with a transition toward deeper unconsciousness. Microstate analyses are expected to reveal longer mean durations and reduced repertoire diversity, further reflecting a state of reduced dynamical complexity.

*Specific Aim 3 (SA3): Characterize the effect of in-phase CLAS on δ-waves, in the presence of painful stimulation*. We hypothesize the *in-phase* CLAS will enhance SWA in the presence of nociceptive stimulation, mitigating nociception-induced reductions in *δ*-wave dynamics. We expect this enhancement to be less pronounced than under non-nociceptive conditions, yet sufficient to mitigate nociception-induced reductions in δ-wave dynamics. Specifically, we will assess δ-wave amplitude, slope, frequency, transition frequency, duration, and density, as well as the preservation of spatial coherence across fronto-central regions. Such findings would suggest that CLAS can stabilize cortical δ-waves and counteract arousal-related desynchronization, thereby supporting anesthetic stability and analgesic protection.

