**Figure 3 fig3:**
[figure not shown]
*Timeline of the study protocol*. Following baseline EEG recording in the awake state (5 min), general anesthesia is induced with propofol and remifentanil. Objective 1 includes three stimulation conditions (*in-phase, anti-phase, sham*; 3 min each, with 20 s pauses). Objective 2 involves *in-phase* stimulation with standardized nociceptive input (*Pre-Pain, Pain*, *Post-Pain* epochs). Anesthetic doses, BIS (target 40–60), and NOL (target <10) are maintained stable throughout.

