### Functional analysis

3.4

Beyond univariate analyses, we will characterize the large-scale neural dynamics underlying depth of anesthesia by constructing functional connectivity networks for each stimulation block. Connectivity will be computed using weighted phase lag index (wPLI) (Vinck et al., 2011), where EEG data will first be filtered into canonical frequency bands (delta 1–4 Hz, theta 4–8 Hz, alpha 8–14 Hz, beta 14–30 Hz).

The wPLI isdefined as: 
$\mathrm{wPL}I_{\mathrm{ij}}=\frac{E\{ℑ(C_{\mathrm{ij}})\}}{E\{|ℑ(C_{\mathrm{ij}})|\}}=\frac{E\{|ℑ(C_{\mathrm{ij}})|\mathrm{sgn}(ℑ(C_{\mathrm{ij}}))\}}{E\{|ℑ(C_{\mathrm{ij}})|\}}$
,

where 
$ℑ(C_{\mathrm{ij}})$
 is the imaginary part of cross-spectrum the imaginary component of the cross-spectrum between signals *i* and *j*. The cross-spectrum is defined as C_ij_ = Z_i_Z_j_, with Z_i_ and Z_j_ denoting the Fourier spectrum of channel *i* and the conjugate spectrum of channel *j*. The wPLI values range from 0 (no consistent lag/lead relationship) to 1 (perfect non-zero phase locking) (Vinck et al., 2011).

To assess the directionality of functional connectivity, we will compute the directed phase lag index (dPLI) (Stam and Van Straaten, 2012). The instantaneous phase of each EEG channel will be extracted using a Hilbert transform. For each time point *t*, the phase difference between channels *i* and *j* will be computed as 
$\Delta \phi_{t}=\phi_{i,t}-\phi_{j,t}$
.

The dPLI is then given by: 
$\mathrm{dPL}I_{\mathrm{ij}}=\langle H(\Delta_{\mathrm{\varphi t}})\rangle$
,

where *H(x)* is the Heavyside step function: 
H(x)=1ifx>0,H(x)=0.5ifx=0,andH(x)=0
 otherwise. dPLI values >0.5 indicate that channel *i* consistently leads channels *j*, whereas values <0.5 indicates the opposite.

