### Micro-state analysis

3.6

To examine the fast temporal dynamics of large-scale cortical activity, we will perform an EEG microstate analysis. Microstates represent brief, quasi-stable scalp potential topographies thought to reflect coordinated activity within distributed neural networks (Lehmann et al., 1987; Michel and Koenig, 2018). Global field power (GFP) peaks will be identified from bandpass-filtered data, and the corresponding maps will be clustered using k-means to extract four canonical microstate classes (A-D) (Koenig et al., 2002). The continuous EEG will then be back-fitted to these templates to derive standard temporal parameters: mean duration, occurrence rate, coverage, and transition probabilities.

Comparisons across depth of anesthesia and stimulation blocks will reveal whether CLAS alters the stability or sequencing of cortical microstates, providing a complementary perspective to the spectral and connectivity analyses.

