### Network-level and microstate predictions

4.4

Functional connectivity analyses are expected to reveal more locally coherent *δ*-band activity but reduced large-scale integration during *in-phase* CLAS. Specifically, we anticipate decreased frontoparietal connectivity and lower global efficiency, accompanied by increased modular segregation and modest reductions in small-worldness relative to *anti-phase* and *sham* conditions. This pattern would extend prior findings that anesthetic-induced unconsciousness is associated with breakdown of large-scale network integration, particularly within fronto-parietal circuits (Boveroux et al., 2010; Bonhomme et al., 2016; Lee and Mashour, 2018), and would test whether strengthening δ-waves further accentuates this network fragmentation.

At the level of EEG microstates, we expect *in-phase* CLAS to be associated with longer mean microstate durations, increased coverage of “unconsciousness-associated” classes, and a reduced repertoire of transitions compared with *anti-**phase* and *sham* stimulation (Koenig et al., 2002; Lehmann et al., 1987; Michel and Koenig, 2018). Such changes would indicate greater temporal stability of large-scale cortical states, complementing spectral and connectivity markers of a more deeply unconscious network configuration.

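### SA2's network and microstate measures have no reference state in the study that would let an in-phase versus sham difference be read as deeper unconsciousness, and the protocol predicts opposite directions for two of them

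*Protocol article*

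**What the plan says.** Section 3.1 (EEG pre-processing) gives a closed, numbered list of segments: "Data will then be segmented into the 6 conditions of study: (1) *In-phase*; (2) *Anti-phase*; (3) *sham*; (4) *Pre-Pain*; (5) *Pain*; (6) *Post-Pain".

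The Figure 3 caption describes one further recording: "Following baseline EEG recording in the awake state (5 min), general anesthesia is induced with propofol and remifentanil". Of the period under anesthesia it says: "Anesthetic doses, BIS (target 40–60), and NOL (target <10) are maintained stable throughout".

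On the analyses, section 3.6 states: "Comparisons across depth of anesthesia and stimulation blocks will reveal whether CLAS alters the stability or sequencing of cortical microstates". Section 3.4 states: "we will characterize the large-scale neural dynamics underlying depth of anesthesia by constructing functional connectivity networks for each stimulation block".

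On interpretation, SA2 in section 1.8 expects "reduced network integration, and increased modular segregation, consistent with a transition toward deeper unconsciousness". Section 4.4 expects in-phase stimulation to bring "increased coverage of “unconsciousness-associated” classes".

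Section 3.7.2 makes BIS the depth measure. It compares BIS across the three Part 1 blocks, correlates it with δ-wave amplitude, slope and spectral power, and examines the aperiodic component in relation to it.

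**The concern.** A comparison with sham shows whether stimulation changes a measure. It does not show whether the change is toward deeper or lighter anesthesia. That second step needs evidence that the measure moves in a known direction with level of consciousness, preferably in the same patients and through the same processing. For wPLI, dPLI, the graph measures and the microstate parameters, no analysis in the article supplies it.

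Without a direction established in the data, the reading depends on which prediction is cited, and the article offers two opposite ones. A statistically clear difference in global efficiency could be presented as confirmation whichever sign it has.

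**Working it through.** No test statistic or sample size figure is involved. The check is a comparison of passages plus a count.

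**1. Is there a depth factor among the analysed segments?**
- Segments listed in 3.1: 6. Awake segments among them: 0.
- Targeted depths across the six: 1 (stable doses, BIS target 40–60, Figure 3 caption).
- Segments entering the SA2 block comparison: 3 (in-phase, anti-phase, sham).

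The sentence in 3.6 names two things to compare across, depth and stimulation block. Only block exists as a planned factor. Section 3.4 likewise speaks of depth but builds networks per block.

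**2. How much recording has no stated role?**
- Part 1: 3 × 3 min plus 20-s pauses. This is 9 min 40 s with two pauses or 10 min with three; the article states 10 min.
- Part 2: 1 + 0.5 + 5 = 6.5 min, as the article states.
- Awake baseline: 5 min.
- Total: 5 + 10 + 6.5 = 21.5 min. The awake share is 5 / 21.5 ≈ 23%.
- Over the planned sample: 30 × 5 = 150 min.

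Sections 3.2 to 3.7.3 contain no analysis that uses this recording.

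**3. What could serve as a depth reference for each SA2 measure?**

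| Measure | Compared with sham | Linked to BIS in 3.7.2 | Awake reference |
|---|---|---|---|
| δ-wave amplitude, slope, spectral power | yes | yes | no |
| Aperiodic component | yes | yes | no |
| wPLI, dPLI | yes | no | no |
| Global efficiency, clustering, modularity, small-worldness | yes | no | no |
| Microstate duration, occurrence, coverage, transitions | yes | no | no |

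The last three rows have a comparator but nothing that gives the comparison a direction in terms of depth.

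**4. Can the microstate class prediction be tested?** Section 3.6 extracts four canonical classes, A to D, by k-means. Section 4.4 predicts more coverage of classes tied to unconsciousness. No step says which of the four those are or how they would be found.

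**5. Are the predicted directions consistent?**

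| In-phase stimulation | Section 4.4 | Discussion (section 5) |
|---|---|---|
| Global efficiency | lower | may increase |
| Small-worldness | modestly reduced | preserved |
| Network integration | reduced | preserved integration listed among results that would inform the debate |

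SA2 in section 1.8 agrees with section 4.4, so the Discussion contradicts both.

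**The case against.** A reader might infer that SA2 as a whole has no anchor within the study and that its meaning rests entirely on other work. The documents do not support that. Sham is a within-subject comparator (2.1.3). BIS is a concurrent depth index, compared across blocks and related to δ-wave features and the aperiodic component (3.7.2). It is a weak anchor, because it is derived from the EEG, is held to a target range, and by the article's own account partly reflects the slow activity that stimulation is meant to change. It is still an anchor for those measures.

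Other points on that side:
- **Depth may vary at a fixed target.** Section 2.2.2 allows gradual deepening and section 1.4 says nociception can alter hypnotic depth. One depth is therefore true of the target only. But drift is not a planned level, it runs along a fixed block order, and the pain epochs all fall under in-phase stimulation and belong to SA3. Neither gives the comparison promised in 3.6.
- **The language is hedged.** Section 1.8 calls the work inferential with respect to consciousness, section 4.2 treats BIS as a correlate only, and section 4 presents its predictions as drawn from existing literature. This softens the depth reading but does not remove it from SA2 or 4.4, and it does not resolve the opposing predictions.
- **Details may be in a fuller document.** This is fair for template fitting, and the article nowhere says the awake recording is discarded. The mismatch between a closed list of segments and a promised depth comparison, and the conflict between 4.4 and the Discussion, are in the text shown.
- **Awake versus sham is an imperfect reference.** This stands. The two states differ in propofol, neuromuscular block, possible residual remifentanil, and earphones and earmuffs. A change from awake to anesthetised does not prove that the same direction means deeper within anesthesia. Expressing stimulation effects as a fraction of that change would assume a common scale that nothing in the article supports.

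**Conclusion.** The point holds for SA2's network and microstate measures. They have no within-study reference state for a depth reading, the comparison across depth in 3.6 cannot be formed from the six segments in 3.1, the classes named in 4.4 are identified by no step, and 4.4 and the Discussion predict opposite results for global efficiency and small-worldness.

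The consequence is limited to interpretation. Contrasts of in-phase with sham remain estimable, and neither the primary objective (SA1) nor SA3 depends on this point. No bias or loss of power is claimed; the 150 minutes measures available data, not error. The broader reading, that SA2 lacks any anchor, fails because of sham and BIS.

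The conclusion assumes that the six segments in 3.1 are the complete analysed set, as the numbered list indicates, and that no unseen document assigns the awake recording a role.

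**What to change.** Choose one of two routes.

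**Use the awake recording.**
- In 3.1, add the awake baseline as a reference segment.
- In 3.6 and 3.7.2, report awake versus sham for each network and microstate measure, using segments of equal length. Sham lasts 3 min, so at most 3 of the 5 awake minutes enter.
- Define the unconsciousness-associated classes as those whose coverage rises from awake to sham.
- Describe an in-phase minus sham change as toward deeper or lighter only for measures that clearly move between awake and sham.
- State that this is a two-state directional check and not a graded depth scale, and do not scale effects to the awake–sham difference.

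**Or narrow the claim.** Remove the reference to anesthetic depth from the comparison sentence in 3.6, and limit SA2's network and microstate conclusions to differences versus sham.

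Under either route, reconcile section 4.4 with the Discussion so that each network measure has one predicted direction before data are analysed.

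Cost: the first route needs analysis work only, on data the timeline already collects. The awake segment precedes neuromuscular block and will need extra cleaning for blinks and muscle activity, and some measures may prove not to be interpretable as depth. The second route is a text edit.
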